**Methods:**

This study is a randomized controlled trial (RCT) with blinded assessment comparing Standard Care (SC) with a novel Family Nurture Intervention (FNI). FNI targets preterm infants born 26-34 weeks postmenstrual age (PMA) and their mothers in the NICU. The intervention incorporates elements of mother-infant interventions with known efficacy and organizes them under a new theoretical context referred to collectively as calming activities. This intervention is facilitated by specially trained Nurture Specialists in three ways: 1) In the isolette through calming interactions between mother and infant via odor exchange, firm sustained touch and vocal soothing, and eye contact; 2) Outside the isolette during holding and feeding via the *Calming Cycle*; and 3) through family sessions designed to engage help and support the mother. In concert with infant neurobehavioral and physiological assessments from birth through 24 months corrected age (CA), maternal assessments are made using standard tools including anxiety, depression, attachment, support systems, temperament as well as physiological stress parameters. Quality of mother-infant interaction is also assessed. Our projected enrolment is 260 families (130 per group).

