Mothers complete initial assessments after consent and families are then assigned to the FNI intervention group or the SC group using a randomized block design. For randomization, six group assignment cards (3 FNI: 3 SC) are placed in envelopes and sealed. The envelopes are shuffled, numbered and placed in a packet prior to use. The RA withdraws an envelope from the packet to determine group assignment. Within 1 to 2 days of consenting, mothers assigned to the FNI group meet with a Nurture Specialist (NS) designated to facilitate the intervention and begin to carry this out, as described in the Intervention Methods section below. Mothers of infants assigned to the SC condition receive NICU standard care as described in the Standard Care section below. Twins are "clustered" for purposes of randomization, with both infants being assigned to the same group along with the mother.

To determine the total sample size necessary to ensure statistical power of not less than 0.8 to detect differences between group means, we considered the detectable difference for each of the primary outcome variables that would be of interest for a successful study result. Our experience and that of others suggested that effect sizes within the 'medium' range would be achievable (i.e., 0.4 to 0.6). Therefore, given the two independent samples created within the RCT design, assuming a significance level of α = .05 for a two-tailed test, we estimate that we will have at least 80% power (1-*β *≥ .80) to detect a difference between groups for effect sizes and total sample sizes as described in Table 1. Experience with the pilot study suggests that we could expect attrition at a rate as high as 40%. To accommodate this, we intend to recruit a total of N = 260 participants from which a final sample size sufficient to detect all differences of interest should be achieved.

**Table 1 T1:** Power analysis

Outcome Measure	PMA	Reference Population *μ *(*σ*)	Detectable Difference |*μ*_FN_-*μ*_SC_|	Effect Size *d*	Total N Required

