**Infant**					
**EEG **[**73**]	Term	6.044 (.434)	0.2	.46	150
**NNNS **[**88**]*****	Term	4.32 (1.73)	1.0	.58	96
**HRV **[**22**]	Term	1.77 (1.10)	0.5	.45	154
**Bayley-III **[**69**]	18 months	96.4 (14)	6.0	.41	174

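### At the 40% attrition it is meant to absorb, a recruitment of 260 leaves 156, fewer than Table 1 requires for Bayley-III (174) and maternal cortisol (186)

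*Protocol article*

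**What the plan says.** The sample-size paragraph (Methods and Design, Participants) aims to "ensure statistical power of not less than 0.8 to detect differences between group means", "assuming a significance level of α = .05 for a two-tailed test". It then allows for loss: "Experience with the pilot study suggests that we could expect attrition at a rate as high as 40" per cent. The recruitment target is presented as the answer to that loss: "we intend to recruit a total of N = 260 participants from which a final sample size sufficient to detect all differences of interest" is expected. The Abstract (Methods) gives the same number in another unit: "Our projected enrolment is 260 families (130 per group").

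Table 1 lists the total N required for 80% power in each row:
- EEG: 150
- NNNS: 96
- HRV: 154
- Bayley-III at 18 months: 174
- Maternal cortisol at 4 months: 186
- CES-D: 120 or 158, depending on which of two reference populations is used

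The section on primary and secondary outcome measures lists Bayley-III at 18 months among the primary outcomes.

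**The concern.** The paragraph joins three figures that should fit together: a recruitment target, an attrition rate and a set of required sample sizes. Taking the stated attrition off the target gives a number below two of the requirements in the table beside it. The sufficiency claim covers every difference of interest, so one clear shortfall is enough to defeat it.

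The stake is how the results will be read. Bayley-III is the latest outcome in Table 1, so losses have the longest time to accumulate there. A reader of a null Bayley-III result would take it as a test with at least 80% power for a 6-point difference. At the attrition the plan says it has allowed for, that power is not delivered on a count of one infant per family.

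**Working it through.** **Inputs.** From the Participants section: recruitment 260, attrition up to 40%, α = .05 two-sided, power 0.80, two equal groups. From Table 1: differences, SDs, effect sizes and required Ns.

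**1. Reproduce Table 1.** Two-sample t-test with d = difference/SD, unrounded. The first two rows are printed as "6.044 (.434) 0.2 .46 150" (EEG) and "4.32 (1.73) 1.0 .58 96" (NNNS).

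| Row | d | N recomputed | N in Table 1 |
|---|---|---|---|
| EEG | 0.2/0.434 = 0.461 | 150 | 150 |
| NNNS | 1.0/1.73 = 0.578 | 96 | 96 |
| HRV | 0.5/1.10 = 0.455 | 154 | 154 |
| Bayley-III | 6/14 = 0.429 | 174 | 174 |
| CES-D, first reference | 5/9.67 = 0.517 | 120 | 120 |
| CES-D, second reference | 5/11.1 = 0.450 | 158 | 158 |
| Maternal cortisol | 0.40 (printed) | 200 | 186 |

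Six of the seven rows reproduce exactly, so the method is the plan's own. Two inconsistencies appear. The printed Bayley-III d of .41 is not 6/14 = .43; at .41 the requirement would be 190. The cortisol N of 186 does not follow from d = .40; it corresponds to d ≈ .413. The cortisol row gives a median and IQR, so its derivation cannot be rebuilt from the document.

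**2. Retained sample.** 260 × (1 − 0.40) = 156, or 78 per arm.

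**3. Compare with the required N.**
- Met: EEG 150, NNNS 96, HRV 154, CES-D first reference 120.
- Short: Bayley-III 174 − 156 = 18; maternal cortisol 186 − 156 = 30.
- Borderline: CES-D second reference 158 − 156 = 2.

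**4. Attrition that 260 can absorb**, 1 − N/260:
- Bayley-III: 1 − 174/260 = 33.1%
- Maternal cortisol: 1 − 186/260 = 28.5%

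**5. Recruitment needed at 40% loss**, N/0.60: Bayley-III 174/0.60 = 290; cortisol 186/0.60 = 310. Multiplying by 1.4 instead of dividing by 0.6 gives 186 × 1.4 = 260.4. That may be where 260 comes from, but this is an inference.

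**6. Power at 78 per arm** (noncentral t, two-sided α = .05, unadjusted):
- Bayley-III: 75.8% at d = 6/14 (72.1% at the printed .41)
- Maternal cortisol: 69.9% at d = .40; 72.7% at d = .413
- CES-D: 79.8% (second reference), 89.4% (first reference)
- Smallest d with 80% power: 0.451; 0.451 × 14 = 6.3 Bayley points

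**7. Twins.** If 260 means families, co-twins add infants at 18 months. The documents give neither the share of twin families (t) nor the within-pair correlation (ρ), so both are assumed here. Counting a singleton as 1 and a pair as 2/(1 + ρ), effective N = 156 × [(1 − t) + 2t/(1 + ρ)].

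| t | ρ | Effective N | Bayley-III power |
|---|---|---|---|
| 20% | 0.9 | 157.6 | 76.2% |
| 20% | 0.5 | 166.4 | 78.5% |
| 40% | 0.9 | 159.3 | 76.7% |
| 40% | 0.5 | 176.8 | 80.9% |

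Maternal cortisol is counted once per mother, so twins do not change it.

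**The case against.** **40% is a ceiling.** The text says "we could expect attrition at a rate as high as 40" per cent, and that a sufficient sample should be achieved. A trial losing 25% would meet every row. That is true, and it limits the claim to attrition above about 28% or 33%. It does not remove the contradiction, because 260 is offered as the number that copes with the ceiling.

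**Twins.** On the families reading, co-twins are assessed at 18 months; the restriction to the first-born applies to the 4- and 12-month visits. This stands in part. At the favourable end of the assumed range Bayley-III just passes 80%, though most of the range stays below. The plan claims no such offset, and it cannot help maternal cortisol.

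**Stronger readings that the documents do not support.** A reader might infer that CES-D fails too. It is short by 2 on only one of two reference rows, at 79.8% power, and the plan does not say that row governs. A reader might also count cortisol as a failed primary outcome. The Table 1 row is maternal, whereas the outcomes section names infant cortisol as primary. Nor is Bayley-III the only long-term primary outcome, since the preschool language scale and the ASQ are listed with it. Finally, a power below 80% does not make a difference undetectable.

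**Conclusion.** The sufficiency statement does not hold at the attrition it is said to cover. It fails clearly for maternal cortisol (156 against 186; power about 70–73%, depending on which Table 1 input is used). It fails modestly for Bayley-III, a primary outcome: 156 against 174, with power about 76% on one infant per family. If co-twins are counted, Bayley-III power is about 76–81%, assuming 20–40% twin families and within-pair correlation 0.5–0.9. The shortfall in numbers rests only on the protocol's own figures; the twin range rests on assumptions. All powers are at unadjusted α = .05. The Planned analyses section applies a Bonferroni correction, which can only lower them.

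**What to change.** Delete the claim that the final sample suffices for every difference of interest, and use one unit, families, in the Abstract and the Participants section. Replacement text could read:

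*With 260 families and 40% attrition, 156 families (78 per group) remain. At two-sided α = .05, unadjusted and before the planned Bonferroni correction, this gives 80% power for d of about 0.45 (6.3 Bayley-III points). Power for a 6-point Bayley-III difference is about 76% counting one infant per family (about 76–81% if co-twins are counted, assuming 20–40% twin families and within-pair correlation 0.5–0.9). Power for maternal cortisol is about 70–73%.*

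In Table 1, reconcile the cortisol entries (d = .40 against N = 186, which implies about .413) and the Bayley-III d (.41 against 6/14 = .43). Then keep a single cortisol power figure.

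The cost is protocol wording and a somewhat less favourable power statement. Changing the recruitment target instead is open to the sponsor, but is not needed to make the text correct.

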**Infant**					
**EEG **[**73**]	Term	6.044 (.434)	0.2	.46	150
**NNNS **[**88**]*****	Term	4.32 (1.73)	1.0	.58	96
**HRV **[**22**]	Term	1.77 (1.10)	0.5	.45	154
**Bayley-III **[**69**]	18 months	96.4 (14)	6.0	.41	174
**Mother**					
**Cortisol **[**89**]	4 months	Median = 2.4	0.45	.40	186
		(IQR: 1.6-4.1)			
**CES-D **[**53**]	4 months	10.24(9.67)[90]	5.0	.52	120
		19.8 (11.1)[91]		.45	158

A power analysis was conducted to determine the sample size needed to ensure statistical power of (1-*β*) = .80.

*Non-optimal reflexes. Illustrative of the 13 NNNS subscales. Citation for the reference population is the same as that for all Outcome Measures except CES-D. Abbreviations: Bayley-III, Bayley Scales of Infant Development, III; CES-D, Center for Epidemiological Studies Depression Scale; HRV, heart rate variability; NNNS, NICU Network Neurobehavioral Scale; PMA, post-menstrual age of the infant.

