### Planned analyses

Descriptive statistics will be derived for all predictor and outcome variables. Family socio-demographic characteristics are not expected to differ by study group, but significance tests will be conducted to confirm the success of the randomization process. Outcomes for the two study groups including infant EEG measures, stress and development, and maternal stress and depression will be compared at each measurement interval (intake, term, 4, 12, 18, and 24 months CA) using independent t-tests for differences between means for continuous data and chi-squared tests for differences between proportions for categorical data. The Bonferroni correction will be applied to account for multiple testing. Longitudinal analyses assessing differences over time will be conducted using repeated measures ANOVA for continuous data and Kruskal-Wallace or Friedman's adaptation of this test for non-parametric data. Generalized linear models will be used to assess the variability in infant development, as measured by Bayley-III Scales at 18 months CA. This variability is explained by repeated maternal and infant psychological and neurological factors after controlling for baseline family socio-demographic characteristics.

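### Table 1's maternal cortisol row is inconsistent with itself and with its reference data: d = .40 needs N = 200, not 186, and neither figure follows from the printed median and IQR

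*Protocol article*

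**What the plan says.** In the protocol article, the sample-size paragraph under Participants sets the framework. It works "given the two independent samples created within the RCT design" and "assuming a significance level of α = .05 for a two-tailed test". For the effect sizes and sample sizes in Table 1 it concludes "we estimate that we will have at least 80% power". The note under the table repeats the aim: "A power analysis was conducted to determine the sample size needed to ensure statistical power of (1-*β*) = .80".

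Table 1 has a column for the reference mean and SD, then the detectable difference, d and total N. The cortisol row, under the Mother heading, puts a median in the mean and SD column and reads "Median = 2.4 0.45 .40 186", with an IQR of 1.6-4.1 on the line below. It is the only row without an SD, and no transformation is mentioned.

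Planned analyses compares the groups at each measurement interval "using independent t-tests for differences between means for continuous data".

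**The concern.** There are two separate problems. First, the printed d and N do not agree with each other under the method that evidently produced the rest of the table. Second, the printed reference data do not yield either figure. The quartiles lie 0.8 below and 1.7 above the median, so the distribution is right-skewed, and its IQR is much wider than d = .40 allows.

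At stake is whether the 80% power statement can be relied on for maternal cortisol at 4 months. If it cannot, a null cortisol result could be given more weight than the design supports. The Methods and Design opening makes decreased stress responses in mother and infant at 4 months a secondary hypothesis, so the consequence is limited to that comparison.

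**Working it through.** **Inputs.** Two-sided alpha .05 and 80% power (Participants; Table 1 note). Two independent groups, allocated 1:1 ("six group assignment cards (3 FNI: 3 SC"). Test: "independent t-tests for differences between means for continuous data". Cortisol: median 2.4, IQR 1.6-4.1, difference 0.45, d = .40, N = 186 (93 per arm). No SD is given.

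**Method.** d = difference / SD. Power and N come from the noncentral t distribution with equal groups. The normal approximation is n per arm = 2(1.960 + 0.842)² / d².

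**Step 1: the table's other rows.**

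| Row | Difference / SD | d | N recomputed | N printed |
|---|---|---|---|---|
| EEG | 0.2 / 0.434 | .461 | 150 | 150 |
| NNNS | 1.0 / 1.73 | .578 | 96 | 96 |
| HRV | 0.5 / 1.10 | .455 | 154 | 154 |
| Bayley-III | 6.0 / 14 | .429 | 174 | 174 |
| CES-D, first reference | 5.0 / 9.67 | .517 | 120 | 120 |
| CES-D, second reference | 5.0 / 11.1 | .450 | 158 | 158 |

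All six match exactly, so the method is identified.

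**Step 2: cortisol, printed d against printed N.** For d = .40 the normal approximation gives 2 × 7.85 / 0.16 = 98.1, so 99 per arm and 198 in total. The t calculation gives 200. Rounding of d does not close the gap: d = .405 still needs 194. A one-sided test gives 156. N = 186 corresponds to d of about .413 to .415. At d = .40 and N = 186, power is 77.4% (77.9% by normal approximation).

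**Step 3: printed d against the printed spread.** The implied SD is 0.45 / 0.40 = 1.125. A normal variable with that SD has IQR 1.349 × 1.125 = 1.52. The printed IQR is 4.1 − 1.6 = 2.5.

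**Step 4: power for 0.45 at N = 186 under different readings.** Each SD below is an assumption, because the article gives none.

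| Reading of the row | d | Power |
|---|---|---|
| Raw, SD from upper half of IQR: 1.7 / 0.6745 = 2.52 | .179 | 23% |
| Raw, lognormal with this median and IQR: SD 2.42 | .186 | 24% |
| Raw, SD = IQR / 1.349 = 1.85 | .243 | 38% |
| Log scale, 2.4 rising to 2.85: ln(2.85/2.4) / 0.698 | .246 | 39% |
| Log scale, 2.4 falling to 1.95: ln(2.4/1.95) / 0.698 | .298 | 52% |
| Raw, SD = IQR / 2 = 1.25 | .360 | 69% |
| Raw, SD from lower half of IQR: 0.8 / 0.6745 = 1.19 | .379 | 73% |

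The log SD is ln(4.1/1.6) / 1.349 = 0.698.

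**Step 5: 0.45 as an undeclared log difference.** In log2 units, SD = 0.698 / 0.693 = 1.006, so d = .45, N = 160, and power at 186 is 86%. In natural-log units, d = 0.45 / 0.698 = .65, N = 78, and power is 99%. Neither gives d = .40 or N = 186.

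**The case against.** The tempting stronger reading is that the trial has 38% power for cortisol and would more likely than not miss a true 0.45 difference. The documents do not support that as a fact. The 38% depends on SD = IQR/1.349, a normal-theory conversion applied to visibly skewed data. Other readings in the median's units run from 23% to 73%, and some exceed one half. The row cites an outside source for its reference population, and the SD or transformation actually used may be there. This objection stands, and it limits the point to figures that disagree and cannot be reproduced.

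A printed d is also imperfect elsewhere. Bayley-III shows .41 with N = 174, whereas 6/14 = .43 gives 174 and .41 would need 190. The step from .40 to about .414 could therefore be a small slip. But the Bayley N can be rebuilt from its own difference and SD, and the cortisol N cannot. A slip of that size would also leave the conflict with the IQR untouched.

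A reader might also infer that a primary endpoint is compromised. Primary and Secondary Outcome Measures lists infant HRV and cortisol as primary, but this row is maternal and mother-infant cortisol appears among the secondary outcomes. That inference is not supported either.

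Lastly, cortisol is sampled four times per session at 4 and 12 months, and Planned analyses also provides for repeated-measures ANOVA and rank methods in the longitudinal analyses. That is fair, but Table 1 sizes a two-group comparison of means. A rank test would not clearly rescue it: in simulated lognormal data with this median and IQR and 93 per arm, a Mann-Whitney test had about 50% power for a 0.45 change.

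**Conclusion.** The point holds as an inconsistency in a stated power calculation. Without any assumption about spread, d = .40 and N = 186 do not belong together: the first needs 200, and the second gives 77.4% power at that effect. Neither figure follows from a median of 2.4 and an IQR of 1.6-4.1.

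The true power for a 0.45 difference is not determined by the article. If 0.45 is in the units of the median, every reading tried falls below 80%, from about 23% to 73%. Only an undeclared log difference lifts it above 80%, and then the printed d and N are still wrong. The direction of the shortfall on the table's own scale is therefore sound, but its size is not known. This is a correction to one secondary maternal row, not evidence that the trial as a whole is too small.

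**What to change.** - State the cortisol scale and units, the SD, and any transformation or IQR-to-SD conversion actually used.
- Recompute d, N and the detectable difference from those inputs, so that the row can be rebuilt like the other six. An SD back-calculated from the IQR under normality should not simply be inserted as if it were a reported value.
- Make the analysis scale match the scale used for power. If a log scale is chosen for skewed cortisol, the printed IQR suggests a log SD of about 0.70. At N = 186 the detectable log difference is then about .414 × 0.698 = 0.289, a ratio of about 0.75 (for example 2.4 to about 1.8).
- Withdraw the 80% power claim for a 0.45 difference unless the restated inputs support it.

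The cost is one table row, a qualifying clause in the sample-size paragraph and, if a log scale is adopted, a word in Planned analyses. No added enrolment or procedures are needed. The stated sensitivity for cortisol may become less favourable.

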### Intervention methods

#### Family Nurture Intervention

FNI is overseen and facilitated by specially trained Nurture Specialists (NS). Currently, these are former NICU nurses, although with proper training FNI could be facilitated by non-RNs. FNI employs three categories of calming activities that are based upon the availability of the infant for nurturing interactions with the mother and upon the availability of the family members to meet with the mother and NS. By including multiple activities, we are able to initiate at least some aspects of the calming intervention very early, when the medical status of the most vulnerable infants precludes more comprehensive approaches.

The intervention procedures in this trial are standardized and are accordingly meant to be replicable. However, the dose of the intervention varies according to the availability of the infant, the mother and the family. Mothers recruited into the study and assigned to the FNI group commit to at least four one-hour intervention sessions a week. However, FNI mothers who come in more frequently will perform these interventions more often. Research nurses facilitate at least the minimum four intervention sessions per week and keep logs of intervention activities and duration. Mothers in both groups also complete logs of weekly nurture activities. All of the nurture and intervention activities are tracked.

The first calming interactions between mother and infant take place while the infant is confined to the isolette. These activities are designed to be compatible with the limited access of the mother to the infant during the initial days in the NICU. For example, during the very first days in the NICU reciprocal odor cloth exchange may be the only way that the mother can begin to establish contact with her infant. Touching and vocal soothing are added as soon as possible. At this stage the intervention is designed to engage the sensory systems of smell, touch, hearing and sight through odor cloth exchange, firm sustained touch, vocal soothing and eye contact.

As the infant's medical status becomes stable and the infant is well enough to leave the isolette for skin-to-skin or non skin-to-skin holding and feeding, the mother is able to engage in *Calming Cycle *sessions as described below. This next stage is designed to engage the sensory systems of taste, temperature, vestibular, and kinesthetic systems in addition to the aforementioned sensory systems.

As the family members become available to meet with the NS and mother, the importance of ongoing calming activities between mother and infant as well as family support for the mother are discussed. These sessions are designed to engage the family members in reassuring and calming the mother and in providing continued support for her when the infant goes home.

